### Data management {19}

An electronic data collection system (EDC) was adopted for online data acquisition in this clinical trial. To ensure the safety and privacy of the original data, the research group will arrange full-time CRC to perform data entry to avoid the issues associated with data transportation. Second, medical coding will be carried out in accordance with CTCAE5.0, MedDRA-23.0, and other reference standards. Data management plans will be designed by the data administrator before the trial, which will include data management plan management, studies on the general situation, such as research purpose, research of the overall design, data management of schedules, rules and responsibilities of the relevant personnel, including the EDC system administrator (Admin), project data manager (DM), the researchers (absence), data operator, and arbitrator (CRA), among others, on design, data management, including database design and logical design verification, distribution of users and access, data processing, data quality control, closed database, data safety and security measures, and EDC system contingency plans. The data administrator will upload the random system designed by the statistician in a prescribed format for screening and randomization to be performed later.

### Confidentiality {27}

Once the recruitment commences, the patients will directly contact the researcher to avoid revealing their personal information to others. The researchers shall not discuss the patients’ condition and information in public areas, and patient data cannot be released in the media or on the internet. All documents will be stored confidentially and will only be accessible to members of the trial team. An EDC was used for online data collection in this clinical trial. We will assign specific permissions to the different groups of researchers in the project to ensure the security and confidentiality of data. All data collected in the system will be backed up with reliable data and privacy security mechanisms, and desensitization technology will be adopted to ensure absolute privacy of the data of project participants. All data collected during the study will remain strictly confidential and only be accessed by researchers; the data will be made available to other researchers upon request after the analyses and publication of primary findings. In addition to the patient’s initials, the patients’ outpatient or inpatient number will also be recorded in the CRF during the trial: “Patient initials will be recorded on the CRF cover and information page, not signatures or names.” Even if the initials are duplicated, the outpatient or inpatient number can be used as a unique ID to identify the relevant information. All original data will be recorded in the study medical records and entered in the EDC by the assigned access researcher.

### Plans for collection, laboratory evaluation, and storage of biological specimens for genetic or molecular analysis in this trial/future use {33}

Not applicable.

## Statistical methods

### Statistical methods for primary and secondary outcomes {20a}

Data analysis will be completed using the Statistical Packages of Social Sciences software (version 24.0). Qualitative indicators will be described in terms of frequency tables, percentages, or component ratios, whereas quantitative measures will be described in terms of mean, median, lower quartile (Q1), upper quartile (Q3), minimum, and maximum. For the comparative analysis of the two groups, the chi-square test, Fisher’s exact probability method, and Wilcoxon rank and inspection will be applied for qualitative data and *t* test will be applied for quantitative data, while the *t* test will be applied for quantitative data with normal distribution. Homogeneity test of variance will be conducted among the groups, with a cutoff level of 0.05, and the Satterthwaite method will be used to conduct the corrected *t* test when the variance is uneven. If the data do not follow normal distribution, the Wilcoxon rank test and inspection will be performed. The two-sided test will be uniformly used in the hypothesis test, and the test statistics and their corresponding *P* values will be provided, with *P* values ≤ 0.05 considered statistically significant and *P* values ≤ 0.01 considered highly statistically significant.

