**Methods:**

A randomized, double-blinded, placebo-controlled clinical trial was proposed. A total of 122 patients with HFpEF will be randomly assigned to receive Zhigancao Tang granules or placebo for 12 weeks. The primary outcome measure is cardiac function. The secondary outcomes include measurement of the integral TCM syndrome score, echocardiography, 6-min walk test, N-terminal-pro hormone B-type natriuretic peptide level, atrial natriuretic peptide level, Minnesota Living with Heart Failure scale, and Lee’s scale. The outcome measures will be evaluated at baseline, 4 weeks, and 12 weeks. Adverse events will be evaluated from baseline till the 12-week follow-up period.

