### Outcomes {12}

#### Primary outcome

Cardiac function (from baseline to weeks 4, 12, and 24)
◦ Significant effects: cardiac function restored to level 1 or increased by level 2◦ Effective: heart function improved to level 1, but not to level 2◦ Invalid: no change in cardiac function◦ Deterioration: decrease in cardiac function by a single grade or more

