#### Secondary outcomes

Echocardiography (from baseline to weeks 4 and 12): Echocardiographic measurement of LVEF, left ventricular end diastolic diameter (LVEDd), left ventricular end-systolic diameter (LVESD), ratio of left ventricular early diastolic fast filling peak to late diastolic filling peak (E/a), and ratio of early diastolic velocity of mitral valve to early diastolic annular velocity (E/e) [11].Lee’s scale (from baseline to weeks 4, 12, and 24)
◦ Significant effect: decrease in score by > 75% after 12 weeks◦ Effective: decrease in score by 50%–75% after 12 weeks◦ Invalid: decrease in score by < 50% after 12 weeks◦ Aggravation: score is unchanged or higher than the score recorded before the treatmentThe Minnesota Living with Heart Failure Questionnaire (MLHFQ) scale (from baseline to weeks 4, 12, and 24): The symptoms of heart failure substantially affect patients, and the MLHFQ scale is used worldwide to assess the quality of life in patients with heart failure [12]. The MLHFQ scale, consisting of 21 questions related to physical and emotional changes, will be used to assess the impact of heart failure on the quality of life in the last 4 weeks. Higher scores indicate worse outcomes. Patients will be assessed based on the scale before and after the trial.Six-minute walking test (from baseline to weeks 4, 12, and 24): This test is a measure of the greatest distance the patient can traverse by walking on a hard ground without obstacles within 6 min at the fastest possible speed. It provides a comprehensive assessment of the exercise capacity of the patient. The differences in the distance covered by the patients in each group will be observed before and after the treatment to evaluate their exercise endurance and quality of life.NT-proBNP, ANP (from baseline to weeks 4 and 12): NT-proBNP is a reliable and sensitive indicator of heart failure. Its elevation is positively correlated with the severity of heart failure. Changes in the levels of NT-proBNP and ANP in each group will be measured before and after treatment.Integral TCM syndrome score (from baseline to weeks 4 and 12; the scores and details are presented in Tables 2 and 3): A scale of 0–6 points and half quantitative points will be used to score the patients according to the severity of clinical symptoms.

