## Assignment of interventions: allocation

### Sequence generation {16a}

The ResMan clinical trial public will be used as the central randomization tool to automatically generate random numbers. Participants will be required to register once they meet the inclusion criteria. Each participant will be provided an ID as a unique identification number and assigned to one of the two groups by logging on to the website of the randomization center.

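### Outcomes with a recorded baseline are compared by unadjusted two-group tests; the tests are valid, but they give up precision and handle chance baseline imbalance poorly

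*Protocol article*

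**What the plan says.** The section on statistical methods for primary and secondary outcomes {20a} fixes the between-group tests. For qualitative outcomes, "the chi-square test, Fisher’s exact probability method, and Wilcoxon rank and inspection will be applied for qualitative data". For quantitative outcomes, the t "test will be applied for quantitative data with normal distribution". The choice between forms of the t test depends on a preliminary test: "Homogeneity test of variance will be conducted among the groups, with a cutoff level of 0.05", with the Satterthwaite version used when variances differ. For other quantitative data, "If the data do not follow normal distribution, the Wilcoxon rank test and inspection will be performed". None of these takes a covariate or a stratum, and no ANCOVA, regression, stratified test or mixed model is named anywhere in the article.

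The baseline values will be available. The abstract states "The outcome measures will be evaluated at baseline, 4 weeks, and 12 weeks", and Table 4 marks every efficacy outcome at week 0. Several outcomes are defined relative to baseline. The primary outcome is a graded change, "Cardiac function (from baseline to weeks 4, 12, and 24"). Lee's scale and the TCM syndrome score are graded by percentage reduction, the walking test is described through before/after differences, and for the peptides, "Changes in the levels of NT-proBNP and ANP in each group will be measured before and after treatment". The inclusion criteria admit NYHA classes I to III.

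**The concern.** Baseline level usually predicts follow-up level in measures such as walk distance, MLHFQ score, echocardiographic dimensions and natriuretic peptides. A test without the baseline as covariate then has a larger standard error than the data require. It also gives an estimate that moves with whatever baseline difference chance produces. With about 51 evaluable patients per arm, that difference need not be small.

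The primary outcome has a related problem. Response is graded by NYHA classes gained or by reaching class I, so the starting class limits which category a patient can reach. A class II patient who gains one class arrives at class I; a class III patient with the same gain does not; a class I patient has no class to gain. An unstratified comparison does not separate these groups.

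At stake are the width of the intervals and the credibility of the estimates if the arms differ at baseline.

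**Working it through.** **The plan's own figure.** Inputs from Sample size {14}: response rates 93.3% and 73.3%, alpha 0.05 (two-sided per {20a}), power 80%. With the unpooled formula,

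n = (1.96 + 0.8416)² × [0.933 × 0.067 + 0.733 × 0.267] / 0.20² = 7.849 × 0.2582 / 0.04 = 50.67, rounded up to 51 per group.

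This matches the stated 51 and confirms that the trial was sized on an unadjusted comparison of two proportions.

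**Variance for quantitative outcomes.** Assume equal SDs at baseline and follow-up and a correlation ρ between them. The article does not give ρ, so a range of 0.3 to 0.8 is shown. In units of the variance of a final-value comparison, the factors are: final value 1; change 2(1 − ρ); ANCOVA 1 − ρ². ANCOVA relative to change is therefore (1 + ρ)/2.

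| ρ (assumed) | ANCOVA | Final value | Change | ANCOVA below final | ANCOVA below change |
|---|---|---|---|---|---|
| 0.3 | 0.91 | 1 | 1.40 | 9% | 35% |
| 0.5 | 0.75 | 1 | 1.00 | 25% | 25% |
| 0.7 | 0.51 | 1 | 0.60 | 49% | 15% |
| 0.8 | 0.36 | 1 | 0.40 | 64% | 10% |

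**In patients and power.** At ρ = 0.5, 51 per arm with adjustment are worth 51 / 0.75 = 68 without it. An unadjusted comparison with 80% power would, with ANCOVA, have power of about Φ(2.80 / √ratio − 1.96). Against final values this is 83.6%, 89.9%, 97.5% and 99.7% for the four correlations; against changes it is 93.5%, 89.9%, 86.0% and 84.0%.

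**Chance imbalance.** With 51 per arm, the standard error of a baseline difference is √(2/51) = 0.198 SD, so the 1.96 SE limit is 0.39 SD. Given such a difference d, a final-value comparison is shifted by ρd and a change comparison by −(1 − ρ)d. At ρ = 0.5 these are +0.19 SD and −0.19 SD. ANCOVA removes the shift in expectation.

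**Primary outcome.** Under the planning rates, expected non-responders are 51 × 0.067 = 3.4 on treatment and 51 × 0.267 = 13.6 on control, about 17 in all, spread over up to three NYHA classes. An illustrative simulation at these rates, using logistic regression on a generic baseline covariate (not NYHA class itself), gave about 80% to 82% power unadjusted. Adjusted power was 83%, 84% and 89% at assumed log odds ratios of 0.5, 1.0 and 1.5 per SD. Up to 12 of 1500 runs failed to fit and were counted as non-significant, so these figures are approximate. They indicate a modest gain and some fragility.

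**Variance pre-test.** With n patients in each arm, the pooled and Satterthwaite standard errors are both √[(s₁² + s₂²)/n]. Only the degrees of freedom differ, so the pre-test has little effect unless dropout makes the arms unequal.

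**The case against.** The strongest reply is that nothing here is invalid. Under randomisation the unadjusted tests keep their type I error, and the primary comparison agrees with the sample size calculation. That stands: the issue is precision and conditional bias under chance imbalance.

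A reader might infer that the plan makes no use of baseline and leaves imbalance wholly uncorrected. The Outcomes section {12} does not support this. The primary grading, the percentage reductions, the walk differences and the peptide changes are all built from the baseline value. For walk distance and the peptides the relevant gain is the change-score column: 15% at ρ = 0.7, not 49%. The variance factors do not carry over to the graded percentage reductions.

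A reader might also infer a formal normality pre-test or a confirmed absence of stratified randomisation. The article makes the rank test conditional on non-normal data but states no normality test. On randomisation it says that a central platform "will be used as the central randomization tool to automatically generate random numbers" and is silent on strata, which a condensed article may leave to the full protocol. Neither is claimed here.

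Finally, covariates are often left to an analysis plan. That would answer the point if {20a} were silent, but it names the tests.

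The objection to logistic regression for the primary outcome also stands. With so few expected non-responders, splitting by NYHA class risks separation, and the estimate becomes a conditional odds ratio.

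**Conclusion.** The point holds as an improvement to a stated method. For quantitative outcomes, adjusting for the recorded baseline lowers variance by 9% to 64% against final values and by 10% to 35% against changes, over an assumed correlation of 0.3 to 0.8. The size depends on that correlation and on similar SDs at the two visits, neither of which the article gives. Apart from one degree of freedom, ANCOVA costs nothing relative to either alternative across this range.

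For the primary outcome the case rests mainly on baseline class limiting the reachable category. The expected gain in power is smaller, and no exact figure can be given without the NYHA distribution at entry. The variance pre-test is a minor matter. None of this supports a claim of inflated type I error from omitting baseline.

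**What to change.** - Quantitative outcomes (walk distance, MLHFQ, echocardiographic measures, and NT-proBNP and ANP on the log scale): make ANCOVA at week 12, with the baseline value as covariate, the main analysis, or use one repeated-measures model over the scheduled visits with the same covariate. Keep the t or Wilcoxon test as a sensitivity analysis.
- Primary responder outcome: use a Mantel-Haenszel test stratified by baseline NYHA class (I, II, III), in preference to logistic regression.
- Wherever a t test is kept, use the Satterthwaite version throughout and drop the variance pre-test.

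The cost is wording in the protocol and analysis plan. The methods are available in the SPSS software already named, and no extra data or visits are needed. Because the article describes analysis beginning when the sample reaches 60, the change should be dated, with a statement of whether any between-group results had been seen by then.

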#### Missing data

Any missing data will be treated as a failure using the intention-to-treat principle, and the reason will be recorded.

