### Sample size {14}

The sample size for this study was calculated based on the expected value of efficacy, according to the clinical trial results and analysis of data from previously published articles [13]. The total efficacy rates in the study and control groups were 93.3% and 73.3%, respectively. The significance level (alpha) was set at 0.05, and the statistical power was set at 80%. Based on our calculation, using the PASW statistical software (V.18.0), the experimental and control groups will each require a sample size of 51 patients. Considering a 20% loss to follow-up, 61 participants are required in each group. Therefore, this trial will require at least 122 participants in the current study.

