### Procedure for unblinding if needed {17b}

For emergency blinding, there will be an emergency envelope for every case, with information about the coding and groups. It is necessary to be aware of the drugs used by the patients in case of any serious event, and patients need to be treated. The project leader decides to initiate unblinding and open the corresponding emergency envelope. Once the emergency envelope is opened, the case is treated as a shedded case.

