### Methods in analysis to handle protocol non-adherence and any statistical methods to handle missing data {20c}

We will perform per-protocol and intention-to-treat analyses. Participants with poor compliance (compliance of experimental drug < 80%) or those no longer receiving medication and undergoing testing during the study will be excluded from the per-protocol analysis. Researchers will be advised to take active measures to complete the last test if the participants drop out of the trial or are lost to follow-up for the intention-to-treat analysis. Missing data will be imputed using a multiple imputation procedure via chained equations.

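### Two unqualified missing-data rules conflict (missing = failure; multiple imputation), leaving the handling of a missing primary outcome open; under the failure rule, power at the planned 20% loss is about 46%, not 80%

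*Protocol article*

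**What the plan says.** The protocol article gives two rules for missing data.

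- **Missing data** (under Statistical methods for primary and secondary outcomes {20a}): "Any missing data will be treated as a failure using the intention-to-treat principle, and the reason will be recorded".
- **Section {20c}** (non-adherence and missing data): "We will perform per-protocol and intention-to-treat analyses", and at the end of the same paragraph, "Missing data will be imputed using a multiple imputation procedure via chained equations".

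No section assigns one rule to the primary outcome and the other to continuous outcomes, to the per-protocol set or to a sensitivity analysis.

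Three other places bear on the point.

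- Sample size {14}: "The total efficacy rates in the study and control groups were 93.3% and 73.3%, respectively". With alpha 0.05 and 80% power, the article then concludes that "the experimental and control groups will each require a sample size of 51 patients". This is raised to 61 per arm for 20% loss to follow-up.
- Unblinding {17b}: "Once the emergency envelope is opened, the case is treated as a shedded case". If this means a dropout, such cases may add to the missing outcomes.
- Interim analyses {21b}: statistical analysis began at 60 patients, and the primary investigator decides on continuation from the results.

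**The concern.** A missing primary outcome is either set to failure or drawn from an imputation model. The article prescribes both, without limits, and both reach the intention-to-treat analysis. This is not detail left to an analysis plan: a plan that follows one sentence departs from the other.

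The failure rule cannot apply to everything it claims to cover. Walk distance, NT-proBNP, ANP, MLHFQ and the echocardiographic measures have no failure category.

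The two rules also estimate different things. Imputation under missing-at-random targets the response rates that would be seen with no loss. Missing = failure targets response and being observed together, so loss shrinks both rates, and a difference in loss between arms enters the treatment effect. The 20% added in {14} treats lost patients only as a reduction in number. It makes no allowance for that shrinkage.

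**Working it through.** **Inputs.** From {14}: p1 = 0.933, p2 = 0.733, alpha 0.05, power 80%, 51 per arm before and 61 after allowance for 20% loss. From {20a}: "The two-sided test will be uniformly used in the hypothesis test". Assumptions: a single time point; success means at least the effective grade; loss is equal in both arms unless stated; no adjustment for the interim look.

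**1. The plan's own figure.** With unpooled variance,

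n = (1.960 + 0.842)² × [0.933×0.067 + 0.733×0.267] / 0.200² = 50.7, so 51 per arm. This reproduces the plan. The pooled-variance formula gives 54. The 61 is 51 × 1.2 = 61.2, rounded down.

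**2. Missing = failure, 20% lost in each arm.** Each rate is multiplied by 1 − 0.20:

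- active: 0.933 × 0.8 = 0.746
- control: 0.733 × 0.8 = 0.586
- difference: 0.160

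Power at 61 per arm, with m = (0.7464 + 0.5864)/2 = 0.6664:

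Φ{[0.160×√61 − 1.960×√(2×0.6664×0.3336)] / √(0.7464×0.2536 + 0.5864×0.4136)} = 46.5%.

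Exact enumeration of the uncorrected chi-square test gives 46.4%. For 80% power, the unpooled formula needs 132.4 per arm and the pooled formula about 135 to 136.

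**3. Multiple imputation under missing-at-random, same loss.** With no auxiliary information, this is worth roughly the observed patients, 61 × 0.8 = 48.8 per arm. The difference stays at 0.200. Power is 76.3% by the normal approximation and 80.2% by exact enumeration with 49 per arm. A simulation (4,000 trials, 20 imputations within arm, Rubin's rules) gave 78.5%.

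**4. Other amounts of equal loss** (normal approximation, 61 per arm):

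| Loss per arm | Missing = failure | Imputation (approx.) |
|---|---|---|
| 0% | 85.1% | 85.1% |
| 5% | 73.9% | 83% |
| 10% | 63.4% | 81% |
| 20% | 46.5% | 76% |

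With both rules applied to the same simulated data under the planned effect, the significance verdict differed in 25% of trials at 10% loss and in 37% at 20% loss.

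**5. Type I error of missing = failure** (73.3% in both arms, 61 per arm, exact uncorrected chi-square). The unequal splits are assumptions; the article gives only an overall 20%.

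| Loss active / control | Rates tested | Rejects |
|---|---|---|
| 20% / 20% | 0.586 vs 0.586 | 5.3% |
| 22.5% / 17.5% | 0.568 vs 0.605 | 7.4% |
| 25% / 15% | 0.550 vs 0.623 | 13.6% |

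In the last row, 13.3 of the 13.6 points favour placebo and 0.3 favour active. Reversing the split reverses these shares. Imputation rejected in about 5.7% of simulated trials under either split.

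**The case against.** The strongest defence is that the wording is a clumsy condensation. Failure has meaning only for graded outcomes (cardiac function, Lee's scale, the TCM score), and imputation suits the continuous ones, so the authors may have intended that split. This is plausible and would settle the matter in one sentence. But the article does not say it: the Missing data sentence covers every missing value, and {20c} does not exempt the primary outcome.

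It can also be said that loss may stay below 20%, because {20c} asks researchers to obtain a last test from dropouts and {18b} provides reminders and travel costs. That stands, and the table shows the smaller gap. At 10% loss the failure rule still costs about 18 points of power against imputation.

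Three stronger readings are tempting, and the documents do not support them.

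- *The rule will be picked after the data are seen.* Nothing says so. An analysis plan not shown may rank the rules, and {21b} does not say whether the interim results are shown by arm. The text only leaves the choice open while interim results exist.
- *Missing = failure produces false claims of efficacy.* With equal loss it does not. With more loss on active, the excess rejections favour placebo; only more loss on control would favour active. No split by arm is stated.
- *Imputation must be primary.* Missing = failure is an accepted primary rule for a responder outcome, provided that the sample size is built on it.

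**Conclusion.** The contradiction is real and reaches the primary analysis. No other section resolves it.

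At the plan's own rates, sample size and loss, the choice of rule moves the targeted difference from 20.0 to 16.0 points and the power from about 76–80% to about 46%. The stated 80% therefore fails if the Missing data section governs. These figures rest on equal loss in both arms, loss unrelated to response within arm, and imputation without auxiliary variables.

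The type I error is a secondary and conditional matter: 5.3% with equal loss, and about 13.6% under an assumed 10-point difference in loss, in the direction set by which arm loses more. The documents support the finding that the rule is not fixed. They do not support a finding that it will be chosen on the results.

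**What to change.** Reconcile the Missing data section with {20c}:

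1. Name one primary missing-data rule for each outcome, and label the other as a sensitivity analysis where it applies.
2. Remove the wording in the Missing data section that covers all missing data. Confine missing = failure to the graded responder outcomes: cardiac function, Lee's scale and the TCM score.
3. Use multiple imputation for the continuous outcomes.
4. If missing = failure is primary for cardiac function, restate the power in {14} on the diluted rates: about 46% at 61 per arm with 20% loss, or about 132 to 136 per arm for 80%. If imputation is primary, report missing = failure as the sensitivity analysis.

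Settle this before any further analysis by arm. The cost is wording and one extra analysis, with no new data to collect. Enrolment changes only if the sponsor keeps the failure rule as primary and wants to restore 80% power.
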